## Setting the nutritional targets

The screenshot shows the 'Nutrition target' page in the GS2 system. At the top, there's a navigation bar with 'Glucose', 'Safe', 'Settings', 'Patients', 'Advice', 'Nutrition target' (selected), and 'System log'. Below this, a patient header shows 'Patient: [name] M 45 yrs, 2 d. ICU, non-diabetic, unknown', 'User: [name] (administrator)', and '00:04:24'. A status bar indicates 'Length of ICU stay: 45 hours', 'Number of nurse shifts: 6', and 'Acuteness factor: 70 %' with an 'apply' button. The main content area is divided into two columns: 'Caloric Target' (highlighted in pink) and 'Protein Target' (highlighted in blue). The 'Caloric Target' column has three sub-sections: 'Indirect Calorimetry' (Last measured: 29/01 15:40, Value (kcal): 2160, 'apply' button), 'Free estimate' (empty input, 'apply' button), and '25 kcal/kg/d' (Weight estimate: 95 kg, BMI: 24.2 kg/m², Ideal Weight: 88.2 kg, 2280 kcal/d, 'apply' button). Below these, 'Current Energy Expenditure (EE)' is 2160 kcal/d. The 'Protein Target' column shows 'Daily requirement: 1.3 g/kg/d', 'Actual weight: 95 kg', and 'Ideal weight: 88.2 kg'. Below this, 'Proteins required' is 124 g/d. The bottom section, 'During recovery phase (post-acute phase)', shows 'Total caloric intake since ICU admission: 71 % of cumulated energy expenditure', 'Recovery factor: --', and 'Final Caloric Target (post-acute phase): --'. The 'Protein Target' column also shows 'On hemofiltration (IHF or CHF):', 'Is HF (CHF or IHF) currently in use? yes', 'Compensation for amino acid (AA) losses: 130 %', and 'Final Protein Target: 112 g/d'.

Figure 6. The page used in GS2 to set the nutritional (caloric and protein) targets.

Nutritional targets are set once every day by the attending physician. To set the nutritional targets the user must provide an estimate of the patient's Current Energy Expenditure (EE) and of the patient's Acuteness factor. The estimated EE is provided by clicking on one of the three "apply" buttons for Indirect Calorimetry, Free estimate or 25 kcal/kg/day. In the example in Figure 6. Indirect Calorimetry has been selected, resulting in an estimate of 2160 kcal/d for EE. The patient's Acuteness factor is provided by typing it (70%) in the Acuteness factor field and clicking "apply". The Acuteness factor is by default set to 20% at admission to the ICU and is automatically increased by 10% at the beginning of each nurse shift, until it reaches 100%. It can be set to any value between 0% and 100% at any time. The Caloric target is then calculated as the product of EE and the Acuteness factor (1512 kcal/d). The Proteins required (124 g/d) are calculated as the Daily requirement (1,3 g/kg/d) multiplied by the patient's weight (or ideal weight, if the BMI is above 25kg/m²). The Protein target (86 g) is then calculated as the Protein Target multiplied by the Acuteness factor. The Final Protein Target (112 g/d) is the same as the Protein Target, unless the patient is on hemofiltration, in which case it is 130% of the Protein Target.

## Advising on nutrition and insulin therapy.

Advice on insulin and nutrition is required every time a new BG measurement becomes available. On the GS2 "Advice" page the user is reminded when the next BG measurement is due. In the example in Figure 7, this is in -30 min, or in other words, the measurement is 30 min overdue. The user should respond by making a BG measurement and reporting it to Centricity. Within 10s GS2 will have imported the measured BG and will replace the "To do" item "BG measurement due" with a new "To do" item "Request new advice".

[figure not shown]

Figure 7. The GS2 "Advice" page which is used to request advice. The page displays the history of insulin therapy, the BG measurements, and simulated and predicted BG (black curve) in the diagram at the top left. The nutrition history is displayed in the bottom left diagram. On the right-hand side, the upper panel shows the current insulin sensitivity of the patient, current "To do" items (user tasks) and when they are due or overdue. Finally, the lower right-hand panel displays the current state of achievement of the caloric and protein intake targets with respect to the ongoing nurse shift, and for the entire day in the ICU.

The user can request advice by clicking the face icon on the middle-left bar. GS2 then shows the advice pop-up (Figure 8). In the example given below, GS2 advises to reduce enteral nutrition (Novasource® GI Forte) from the current rate of 45 ml/h to 35 ml/h. It also recommends starting an amino acid supplement in the form of 15 ml/h Dipeptiven® and stopping the glucose infusion. The advised insulin dose remains unchanged at 1 U/h. The right-side panels show that both the caloric and protein targets are being met. The user can choose to explore other treatment options, or click on "Accept Choice". The user must then set the pumps according to the advice and report the pump settings to Centricity.

[figure not shown]

Figure 8. The GS2 Advice pop-up window, which displays the recommended pump rates for the nutrition and insulin pumps. The two panels on the right display the achievement of calorie and protein targets that were achieved in the figure.

## Calculation of due time for the next blood glucose measurement

GS2 uses the BG prediction error to calculate the maximum time until the next BG measurement is due. The purpose of this is to keep the hypoglycaemia risk at any time below the acceptable risk maximum of 0.05% per measurement, or 2% per patient (under the assumption that one patient has on average about 40 measurements taken, 2% is given by  $0.05\% \times 40$ ). The prediction error is a function of the prediction time, the longer the prediction, the larger is the "uncertainty" of the predicted BG, and thus the "uncertainty curve" has the shape of a "funnel", as can be seen in Fig. 7 above (light-pink shaded area beneath the thicker black line depicting the predicted BG in the upper left-hand plot).

A close-up of Fig. 7 with annotations in text is shown below. The time of the next measurement is when 1) the first time the lower edge of the uncertainty curve reaches the hypoglycaemia threshold, or 2) the next measurement is due according to local department rules, when that is sooner than 1).

[figure not shown]

A close-up of Fig.7 upper left-hand panel: The next BG measurement is due at 20:08, when the lower edge of the uncertainty area (light-pink shaded) the first time touches the hypoglycaemia threshold (dashed horizontal line) after the most recent BG measurement (red squares). The BG target range is depicted as light-green area, and each BG measurement shows the insulin sensitivity that was calculated at the time of the measurement.

In mathematical terms, the "uncertainty curve" at each time  $t$  for the predicted BG concentration is:

$$UC(t) = \exp(\ln \text{predicted BG}(t) + \text{Norm.Inv}(0.0005) * \ln PE(t))$$

where 0.0005 or 0.05% is the "Hypoglycaemia Risk Maximum" setting, i.e., the highest risk of hypoglycaemia deemed acceptable.  $\text{Norm.Inv}(0.0005) = -3.29$  is the inverse of the cumulative normal distribution.

The prediction error PE used to draw the uncertainty curve will be estimated from retrospective data analysis of the historical control group, and the prediction error curve will be drawn and compared to the graph shown in Fig.4. As explained in Section 3.4, the cut-off point to discontinue the trial has been set to the comparison of the graphs on the prediction time at 2 hours, which is expected to be the most frequent interval between BG measurements in hyperglycaemic patients in the acute phase. The rationale for stopping the study is that the uncertainty curve reaches the hypoglycaemia threshold earlier with a larger prediction error, and although the hypoglycaemia risk remains constant, the workload would increase.

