### **1.6 Data Safety Monitoring Committee**

A data safety monitoring committee is not planned for this study. The purpose of the study is "safety and efficacy" of a new medical device. The study terminates in case of: ethical concerns; insufficient subject recruitment; if 5 patients present with two severe hypoglycaemias ( $\leq 2.2$  mmol/l) in the intervention group; 10 device deficiencies which prevent the use of Glucosafe 2 (GS2) for 4 hours; alterations in accepted clinical practice that make the continuation of the investigation unwise; early evidence of benefit or harm of the experimental intervention or because root mean square (RMS) prediction error of GS2 is greater than 26% for predictions of BG 2 hours into the future. Device deficiencies will be handled according to point 5.1 described in the GS2-IB.

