## 3.4 Clinical Evidence to Date for GS2

In the GS2-Clinical Evaluation Report, no clinical testing of GS2 or any equivalent medical device has been identified. Therefore, no claims are currently made for GS2. The performance and safety of GS2 will be assessed through a clinical trial for which a pre-market approval has been applied for at the relevant competent authority.

As mentioned in point 3.3 "Preclinical evidence for GS2", all preclinical tests were performed with Glucosafe, the predecessor of GS2. The predictive accuracy of GS2 will be confirmed by analysis of the historical control group before the prospective phase of the study is initiated.

GS2's predictions of the BG concentrations may be less accurate than assumed. The BG prediction error of GS2 is assumed to match to the error of the GS2 predecessor, Glucosafe (see Section 3.3). The assumed error curve is shown in Fig. 4 below, which was determined by several small retrospective studies [30, 31] of model-based predictions of BG in different ICU patient cohorts (not including ICU-Geneva patients). As with its predecessor Glucosafe, GS2 uses prediction error to calculate the maximum time until the next blood glucose measurement to keep the risk of hypoglycemia below the acceptable maximum risk level (see Section 8.1.1 for details). Thus, a larger prediction error shortens the time to the next measurement, which could ultimately increase the frequency of BG measurements to an unacceptable and undesirable level. From Fig. 4 it can be read that the RMS prediction error of Glucosafe was about 26% for predictions of BG 2 hours into the future. The RMS prediction error will be estimated from the historical control group and a new curve will be drawn to be compared with the curve in Fig. 4. It is expected that GS2 performs equally well or better than its predecessor. If the RMS prediction error of GS2 is greater for the historical control group, the sponsor will decide to discontinue the GS2 study. The cut-off point set to 2 hours is based on the frequency of BG measurements recommended by ICU-Geneva's glycaemic control policies (see Sect.8.1.2).

[figure not shown]

*Figure 4 Maximum acceptable RMS prediction error curve for predictions of BG in the historical control group. The curve is derived from pre-clinical evidence with GS2's predecessor, Glucosafe. For predictions 2 hours into the future, the curve allows the RMS prediction error to be at a maximum of 26%.*

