### 3.5 Justification for the design of the clinical investigation

Reduction of hyper- and hypoglycaemia reduces mortality and adequate nutritional support reduces post-ICU weakness as well as ICU and post-ICU morbi-mortality, as discussed in sect. 3.1. The intended purpose of the study is therefore to assess whether GS2 safely and effectively can reduce hyper- and hypoglycaemia and can bring the achieved nutritional support closer to the nutritional guidelines. The achievement of these study objectives (sect. 4) will be evaluated through the calculation of a number of study outcomes (sect. 5), which will be used to make comparisons between the patients in:

- 1) GS2 intervention group
- 2) Control group
- 3) Historical control group (sect. 3.6)

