### 5.2 Secondary Outcomes

Glycaemic “variability”:

- Mean and SD of BG measurements per day and per patient during the enrolment period
- Maximum of daily BG difference

Achievement of nutritional targets.

- Estimates of energy expenditure, protein requirements, caloric target and protein target are made on a daily basis in the intervention and control groups, as detailed in sect. 8.1.1 and 8.1.2, respectively.
- The caloric target for the day is reached when of 80-100% of the target is achieved.
- The protein target for the day is reached when of 80-100% of the target is achieved.
- Cumulated energy debt, defined as daily energy expenditure minus caloric intake, cumulated over the enrolment period.
- Cumulated protein debt, defined as daily protein requirement minus protein intake, cumulated over the enrolment period.

Prediction of blood glucose (BG)

- Root mean squared prediction error as a measure of the differences between BG predicted by GS2's metabolic model and measured BG. The prediction error will be calculated, as a function of time elapsed since last BG measurement, per patient, per cohort (sect. 9.2.3).

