## **6. CLINICAL INVESTIGATION DESIGN**

### **6.1 General clinical investigation design and justification of design**

This study is an unblinded randomized controlled trial that aims to evaluate the performance and the safety of a new bedside tool: GS2 in comparison to the standard of care.

Data from the historical control group will be analysed retrospectively for 71 patients hospitalized in the ICU at the same period within 2 years before the study. The historical control group is included for two reasons. The first is to be able to assess cross-over effects. These may happen in the randomized control group, if the caregiver's behaviour in this group is influenced by the caregiver's exposure to the GS2 system, when the caregiver is using the system in the intervention group.

The second reason is to confirm the predictive accuracy of GS2. As described in section 3.3.1 there are modest differences between the prediction errors estimated from the three patient cohorts previously analysed with Glucosafe. It is therefore appropriate to confirm that the prediction error of GS2 is similar or smaller compared to Glucosafe's. In case the prediction error is smaller, it will be possible to reduce the frequency of blood glucose measurements, as described in IB 2.5 "Mechanisms of action". The frequency of blood glucose measurements is one of the outcomes for workload (section 9.2.3). This reduces workload and the amount of blood drawn from the patient. In case the prediction error is larger, it is a reason for discontinuation or modifications of the intervention, as noted in Section 2.9.

The analysis of data from the historical control group will start as soon as the authorization of the study has been obtained. Enrolment for the intervention and control groups will start when the retrospective analysis of the historical control group has been completed. Enrolment is expected to take 8 months. The data and the results will then be analysed and submitted for publication.

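### Cheap improvement: the error curve that times GS2 glucose checks is estimated before enrolment in standard-care historical patients, and no scheduled step during enrolment checks prediction error in GS2-treated patients

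*Protocol*

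**What the plan says.** **Source of the curve.** Protocol 8.1.1 (due time for the next measurement) states: "The prediction error PE used to draw the uncertainty curve will be estimated from retrospective data analysis of the historical control group". Under 8.1.2 the historical group is managed by the local protocols, without GS2. Section 6.1 fixes the order: "Enrolment for the intervention and control groups will start when the retrospective analysis of the historical control group has been completed".

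**Purpose of the curve.** It is meant to "keep the hypoglycaemia risk at any time below the acceptable risk maximum of 0.05% per measurement". Sections 3.7 and 8.1.1 turn this into 2% per patient by assuming 40 measurements. The curve does not time every check. A check also falls due when "the next measurement is due according to local department rules, when that is sooner than 1", where item 1 is the moment the lower edge of the curve reaches the hypoglycaemia threshold.

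**Rule on prediction error.** Section 1.6 lists as a reason to terminate that the "prediction error of GS2 is greater than 26% for predictions of BG 2 hours into the future", and 2.9 has the same item. Neither names a group or a time. Section 3.4 names the group: "If the RMS prediction error of GS2 is greater for the historical control group, the sponsor will decide to discontinue the GS2 study". Section 8.1.1 also ties the comparison to the historical data and justifies it by workload, stating that a larger error leaves the hypoglycaemia risk unchanged.

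**Prediction error as an outcome.** Section 5.2 makes it secondary: "The prediction error will be calculated, as a function of time elapsed since last BG measurement, per patient, per cohort". Section 3.5 says of the section 5 outcomes that they are ones "which will be used to make comparisons between the patients in" the three groups. No time point during enrolment is given, and 11.4.4 plans no interim analysis.

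**The concern.** The curve is learned under one treatment policy and used under another. Section 3.3.1 reports that the predecessor's error differed between cohorts, and 6.1 gives this as a reason to confirm the error before starting. The confirmation covers patients of the same ICU, but none treated with GS2.

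If the error in treated patients is larger than the loaded curve, GS2 will place some checks too late for the risk it claims. As the protocol is written, this would first be examined systematically at the final analysis. This is the first study of GS2 in humans (10.3.1), and there is no safety monitoring committee (1.6). The statement in 8.1.1 that risk stays constant with a larger error is true only when the larger error is the one loaded into the device.

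**Working it through.** **1. The plan's own figures.** Norm.Inv(0.0005) = -3.29, as 8.1.1 states. 0.05% x 40 = 2.0%, and 1 - (1 - 0.0005)^40 = 1.98%. Both reproduce.

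**2. Risk at a curve-timed check when the curve does not fit.** I read the prediction-error term in the 8.1.1 formula as the RMS log error defined in 9.2.3. Let r be the true error in treated patients divided by the loaded error. At the due time the threshold lies 3.29 loaded SDs below the predicted value, which is 3.29/r true SDs. The risk is therefore Phi(-3.29/r).

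| r (assumed) | 3.29/r | Risk at a curve-timed check |
|---|---|---|
| 1.0 | 3.290 | 0.05% |
| 1.1 | 2.991 | 0.14% |
| 1.2 | 2.742 | 0.31% |
| 1.3 | 2.531 | 0.57% |

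The protocol gives no value for r. For scale only, the predecessor's 2-hour error ran from 17% to 26% across cohorts (3.3.1), and 26/17 = 1.53. That is a spread between cohorts, not an effect of treatment.

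**3. Would the 26% rule notice, if applied in treated patients?** It fires when loaded error x r exceeds 26%, that is, when the loaded 2-hour error exceeds 26/r:
- r = 1.1: above 23.6%
- r = 1.2: above 21.7%
- r = 1.3: above 20.0%

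Within the 17-26% range either result is possible. With 17% loaded and r = 1.3, the true error is 22.1% and the rule stays silent. With 22% loaded and r = 1.3, it is 28.6% and the rule fires. A fixed 26% is therefore not a test of fit to the curve in use.

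**4. Why per-patient risk cannot be computed.** Take the 2-hour local interval (8.1.2) and an assumed threshold of 3.2 mmol/l. The curve then governs when predicted glucose is below 3.2 x exp(3.29 x PE): 5.60 mmol/l at PE 0.17, 6.18 at 0.20 and 7.53 at 0.26. The share of checks below such a limit depends on the loaded error, the threshold setting and the distribution of predicted glucose in treated patients. The protocol does not give that distribution.

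**5. Precision of a check in the intervention arm.** Assume 40 predictions per patient (the count in 3.7), the same for 71 historical patients, and a design effect of 5 for clustering. The relative SE of an RMS is 1/sqrt(2 x n_eff).
- 20 patients: n_eff = 160, SE 5.6%
- 40 patients: n_eff = 320, SE 4.0%
- 71 historical patients: n_eff = 568, SE 3.0%

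Combining the SEs in quadrature and multiplying by 1.96, the ratio is known to about +/-12% after 20 patients and +/-10% after 40. A ratio of 1.2 or 1.3 is within reach. A ratio of 1.1 often is not.

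**The case against.** **The strongest case against** is that no stated number is wrong, that the historical group is already a site-specific calibration under the same clinical eligibility criteria, and that other layers protect patients:
- caregivers may refuse advice;
- the local rule shortens the interval when it is sooner;
- a malfunction in glycaemia prediction is a device deficiency (10.1), reported to the sponsor within 24 hours (10.3.2);
- advice is checked daily in the run-in and weekly afterwards (7.2.1);
- severe hypoglycaemia and early evidence of harm are stopping reasons (2.9).

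Glucose was also less variable under the predecessor's advice in the two before/after studies of 3.3.3, which, if anything, hints at easier prediction. The device files cited but not shown may contain further controls.

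Much of this stands, and it limits the size of the point. It does not close the gap. The advice check tests conformity with the GS2 settings and clinical acceptability, the deficiency route handles malfunctions, and the stopping reasons respond to events. None of them compares the treated-patient error with the loaded curve.

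**Three stronger readings should be resisted.**
- A reader might apply the risks to all 40 checks and obtain 5.4%, 11.5% and 20.4% per patient at ratios 1.1, 1.2 and 1.3. That assumes the curve times every check, contrary to 8.1.1.
- A reader might estimate the share of curve-timed checks from the predecessor's 7.0 +/- 1.2 mmol/l (3.3.3). Those are measured values. Treating them as predictions and adding 17-20% error puts only about 59-62% of readings in 5-8 mmol/l, against the 76% reported, so the proxy fails.
- A reader might say that the 26% rule could never fire. Step 3 of the working shows that this depends on the loaded error.

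**Conclusion.** The point holds as a low-cost safety improvement, not as an error in a stated figure. The curve on which the 0.05% and 2% justification rests is not scheduled to be checked in GS2-treated patients before the final analysis. The protocol also leaves it unclear whether the 26% rule covers those patients.

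The size that can be supported is conditional: 0.14%, 0.31% or 0.57% in place of 0.05% at a curve-timed check, for assumed ratios of 1.1, 1.2 or 1.3. This rests on log-normal prediction error and on reading the 8.1.1 error term as the RMS log error of 9.2.3. No per-patient figure is supported. A reader might infer that GS2 treatment makes its predictions worse. No document shows this, and the concern is only whether the historical curve carries over to treated patients.

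**What to change.** 1. In 1.6, 2.9 and 3.4, keep the pre-enrolment check. State that the RMS rule also applies to pooled intervention-arm data, calculated by the 9.2.3 method at prespecified points, for example after about 20 and 40 intervention patients. With 1:1 allocation these fall at about 40 and 80 of 142 enrolled, and can coincide with the monitoring visits held about every 10 enrolled patients (12.3).
2. At each point, compare the 2-hour error with 26%. Also compare the error curve up to 2 hours with the loaded curve, with a confidence interval that allows for clustering by patient.
3. If the treated-patient error clearly exceeds the loaded curve, trigger sponsor/PI safety review only. Any change to the curve goes through 2.10.
4. In 8.1.1, qualify the statement that risk is unaffected by a larger error: it holds only if the loaded curve matches the error in treated patients.

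**Cost.** Amendment wording and a few calculations on data already held in the GS2 database, which 8.8 allows to be transferred as they become available. Only intervention-arm prediction errors are used, so there is no between-arm look and no alpha is spent. The downsides are possibly some unnecessary reviews and low sensitivity to small misfits, at a ratio of about 1.1.
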